### Secondary outcome measures

#### Serious clinical events (SCEs)

Time to detection of recurrences and serious clinical events (SCEs) defined as: Colonoscopy-verified recurrence of cancer disease. Increase in CEA measurements shown by repeated measurements. Blood in stool detected by the Hemofec test. Unexplained abdominal pain. Unexplained weight loss of 5 kg during the last three months. Cancer-suspect lesions detected in rectal examination. Lymphandenopathy. Metastatic suspect lesions shown by chest x-ray or ultrasound of liver.

### Sample size

Sample size calculations are according to Campbell's guidelines [15]

Alpha and beta were set at 0.05 and 0.2 respectively and tests were two-sided. We hypothesize that patients followed up by their GP will have a minor to moderate increase in the Global QoL scores (EORTOC-QLQ C30). This moderate effect size equals an increase of 10 units on the Global QOL [16]. Patients with colon cancer (local disease) show a standard deviation of approximately 20 (global QOL) [16]. Allowing for a dropout rate of 20%, to detect this difference with confidence we required a total sample size of 170 patients. Sample size calculations based upon EQ-5D showed similar results [17].

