**Discussion:**

There is an ongoing debate on the best method of follow-up for patients with CRC. Due to a wide range of follow-up programmes and paucity of randomized trials, it is impossible to draw conclusions about the best combination and frequency of clinic (or family practice) visits, blood tests, endoscopic procedures and radiological examinations that maximize the clinical outcome, quality of life and costs. Most studies on follow-up of CRC patients have been performed in a hospital outpatient setting. We hypothesize that postoperative follow-up of colon cancer patients (according to national guidelines) by GPs will not have any impact on patients' quality of life. Furthermore, we hypothesize that there will be no increase in SCEs and that the incremental cost-effectiveness ratio will improve.

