### Objectives

#### Primary objective

We aim to compare quality of life and costs of follow-up among patients followed up by their local GP or at the surgical outpatient clinic. We hypothesize that patients followed up by their GP will experience similar or higher scores on quality of life measures and lower costs during follow-up.

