### Randomization

Randomization will be done at the 1-month check-up (baseline) after the patients have given informed consent. The randomization service is web-based and managed by the Norwegian University of Science and Technology. Patients are stratified according to the Dukes's staging and whether they have a stoma. Patients allocated to general practice follow-up may be referred back to surgical clinics at any point in the study; similarly, patients in the surgeon-led follow-up group are free to consult their GP at any time during the study.

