### Analysis

We will use the intention-to-treat principle when analysing data. Furthermore, we will employ Fayers guidelines to handle missing data [18]. Treatment arms will be compared with respect to potential covariates using continuous and categorical univariable analyses. These will include variables relating to patients (age, sex, comorbidities, cost), treatment (surgical resection, surgical complications, adjuvant therapy), tumour (Dukes's Stage), hospital surgical outpatient clinic (cost, patient satisfaction, QoL), GP practice (cost, patient satisfaction, QoL). The cost elements will include costs related to outpatient visits, GP visits, laboratory tests, radiographs/ultrasound, and examinations due to suspected relapse, treatment of relapse, travelling/transportation, production losses, co-payments and other patient expenses. The net costs and outcomes of the two treatment options will be compared and presented as cost-effectiveness ratios. If the trial reveals no difference in health outcomes or quality of life for the patients, a cost-minimization analysis will be carried out. If we find a difference in quality of life or overall survival rates between the two groups, we will use a cost-utility approach. The economic evaluation will have a societal and health care perspective.

The method of analysis, including adjusting for covariates will comply with the CONSORT statement [19]. The results will be expressed as odds ratios for binary outcomes, hazard ratios for time- to-event outcomes or mean differences for continuous outcomes with corresponding standard errors, 95% confidence intervals, and associated p-values. P-values will be reported to three decimal places with p-values less than 0.001 reported as p < 0.001. For all tests we will use alpha = 0.05 level of significance.

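### The QoL aim is that GP follow-up leaves quality of life unchanged or no worse, but the trial is sized only to detect a 10-unit gain and sets no margin for judging similarity

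*Protocol article*

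**What the plan says.** The protocol article describes the quality-of-life question in four places:

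- **Abstract, Background:** the trial tests whether follow-up can move to the GP with quality of life left unaltered.
- **Abstract, Discussion:** the hypothesis is that follow-up "by GPs will not have any impact on" quality of life.
- **Primary objective:** GP patients "will experience similar or higher scores on quality of life measures and lower costs during follow-up".
- **Sample size:** "We hypothesize that patients followed up by their GP will have a minor to moderate increase in the Global QoL scores", and "This moderate effect size equals an increase of 10 units on the Global QOL". "Alpha and beta were set at 0.05 and 0.2 respectively", and "tests were two-sided". With an SD of about 20 and 20% dropout, the total is 170.

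The Analysis section sets a 0.05 level for all tests and promises mean differences with standard errors, 95% confidence intervals and p-values. It gives no margin against which to read an interval, and nor does any other section.

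The Economic analysis and Analysis sections both make the type of economic evaluation depend on the result. If no difference in health outcomes or quality of life is found, a cost-minimization analysis follows. If a difference is found, a cost-utility analysis follows. Neither section says how the absence of a difference is to be decided.

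**The concern.** A test sized to detect an increase answers a different question from the stated aim. A significant result in favour of the GP arm would contradict the hypothesis of no impact. A non-significant result would show only that a difference had not been demonstrated, which is neither no impact nor similarity. The result that the Abstract hopes for therefore has no criterion by which it could be affirmed.

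This has a practical consequence. Cost-minimization compares costs alone and is justified only if outcomes can be taken as comparable. If that step rests on a test that failed to reach 0.05, a real loss of quality of life in the GP arm could drop out of the economic conclusion.

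Hypothesis, objective and sample-size basis are all stated in this article and do not fit together, so this is not a detail that can be left to an analysis plan.

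**Working it through.** **Inputs.** From Sample size: difference 10, SD 20, two-sided alpha 0.05, power 80%, dropout 20%, total 170. Assumed: 1:1 allocation (no ratio is stated), a single between-arm comparison of Global QoL, and normal approximations.

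**1. The plan's own figure.** n per arm = 2 × [20 × (1.960 + 0.842) / 10]² = 62.8, so 63 per arm and 126 evaluable. Then 126 / 0.8 = 157.5, so 158. The t-test version gives 64 per arm, and 128 / 0.8 = 160. The stated 170 is not reproduced exactly, but it errs on the safe side by 10 to 12 patients and does not affect this point.

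**2. Precision at the planned size.** 170 × 0.8 = 136 evaluable, 68 per arm. SE = 20 × √(2/68) = 3.43. The 95% CI half-width is 1.96 × 3.43 = 6.7 units. Power to detect 10 units is Φ(10/3.43 − 1.96) = 83%.

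An observed difference of exactly 0 would still leave a loss of up to 6.7 units inside the interval. An observed −6.5 would be non-significant, with a lower limit of −6.5 − 6.7 = −13.2, beyond the 10 units that the plan calls moderate.

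**3. Chance of a non-significant result when the GP arm is truly worse by d.** P = Φ(1.96 − d/3.43) − Φ(−1.96 − d/3.43). Only 10 units comes from the plan; 5 and 7 are illustrative.

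| True loss d | P(non-significant) |
|---|---|
| 5 | 69% |
| 7 | 47% |
| 10 | 17% |

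**4. What the planned size supports as non-inferiority.** One-sided 0.025 (lower limit of the two-sided 95% CI), true difference 0, margin M. Power = Φ(M/3.43 − 1.96). Evaluable n per arm for 80% power = 2 × [20 × 2.802 / M]², rounded up, doubled and divided by 0.8. The document gives no margin, so a range is shown.

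| Margin M | Power with 170 randomized | Randomized total for 80% power |
|---|---|---|
| 10 | 83% | 158 |
| 8 | 65% | 248 |
| 7 | 53% | 323 |
| 5 | 31% | 630 |

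**5. Two-sided equivalence within ±10, true difference 0.** Judged by the 95% CI, power = 2 × Φ(10/3.43 − 1.96) − 1 = 66%. Judged by the 90% CI, it is 2 × Φ(10/3.43 − 1.645) − 1 = 80%.

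**The case against.** Several points on the other side have force.

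- **A reader might infer that the plan treats a p-value above 0.05 as proof of equivalence.** No sentence says so. What can be said is narrower: the economic analysis depends on finding no difference, and the 0.05 test is the only criterion offered for it. The promised 95% confidence intervals would support a correct reading, but only against a margin fixed in advance.
- **A reader might count mutually incompatible hypotheses in the objectives and sample size.** The primary objective's wording includes an increase, so it is compatible with the sizing hypothesis in direction. It differs in form, because it asks for non-inferiority. The outright conflict is between the two Abstract statements and the Sample size section.
- **A reader might conclude that the trial is too small.** The figures do not show that. A two-sided test also detects a 10-unit loss with 83% power, and 170 patients suffice if 10 units can be justified as the margin.
- **A reader might add that movement between arms combined with intention-to-treat biases the trial towards similarity, and ask for a per-protocol analysis.** The Analysis section does say "We will use the intention-to-treat principle when analysing data", and the Randomization section says "Patients allocated to general practice follow-up may be referred back to surgical clinics at any point in the study". But return to hospital is part of the strategy under test, and referral is required after a serious clinical event. A per-protocol set based on visits would select patients on events after randomization that may be related to quality of life. No cross-over rate is given, and further analysis sets may be in documents not shown. This is not part of the point.

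After these concessions, the mismatch between aim and sizing, the missing margin and the undefined finding of no difference all remain.

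**Conclusion.** The concern holds in this form: the quality-of-life aim does not match the superiority sizing, no margin is stated, and the cost-minimization switch has no criterion other than a 0.05 test. At the planned size, a non-significant result would be more likely than not if GP follow-up were truly 5 units worse, and nearly an even chance at 7. Following the plan as written could therefore lead to a wrong conclusion of no difference. The defect lies in the hypothesis and the decision criterion, not necessarily in the number of patients.

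The figures rest on SD 20, 136 evaluable patients, equal allocation and a single comparison of Global QoL. How the investigators would in fact interpret a non-significant result is not stated.

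**What to change.** 1. State one primary quality-of-life hypothesis, that GP follow-up is non-inferior to hospital follow-up on Global QoL, and bring the Abstract (Background and Discussion), Primary objective and Sample size sections into line with it.
2. Pre-specify a margin no larger than the plan's own 10 units and justify it. The justification matters: at a 10-unit margin, an observed −3.2 (lower limit −3.2 − 6.7 = −9.9) would pass.
3. Declare non-inferiority only if the lower limit of the two-sided 95% CI for GP minus hospital lies above minus the margin. If it does, test superiority next, with no alpha penalty.
4. Restate power for the chosen margin at zero true difference with 170 randomized, using the second table above.
5. In the Economic analysis and Analysis sections, let the choice of cost-minimization depend on a pre-stated confidence-interval criterion instead of a non-significant test. If that criterion is two-sided, state its power as well.

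**Cost.** With a justified 10-unit margin, this changes wording only and needs no extra patients. The power claim becomes specific to the margin. It falls below 80% at margins of 8 units or less, where the trial would need either more patients (248 at 8 units, 630 at 5) or an open statement of the lower power.

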### Randomization

Randomization will be done at the 1-month check-up (baseline) after the patients have given informed consent. The randomization service is web-based and managed by the Norwegian University of Science and Technology. Patients are stratified according to the Dukes's staging and whether they have a stoma. Patients allocated to general practice follow-up may be referred back to surgical clinics at any point in the study; similarly, patients in the surgeon-led follow-up group are free to consult their GP at any time during the study.

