#### Hospitals

There are three hospital trusts and one university hospital (UNN HF) (in total 11 hospital units) located within the North-Norwegian Health Region. Three hospitals (located in the cities of Harstad, Mo, and Bodø) have an annual volume of more than 20 colon cancer procedures; the University Hospital operates on about 110 patients with suspected CRC cancer annually and approximately 60 of them have a colon cancer disclosed. The University Hospital and these three local hospitals consented to participate. All patients who undergo surgery for colon cancer are followed up at the surgical outpatient clinic at each hospital.

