### Control arm

Patients in the control group consist of patients randomized to regular follow-up at the hospital's surgical outpatient clinic. All these patients are followed up according to the NGICG guidelines. This follow-up is performed by consultants or internship doctors in digestive surgery.

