The geography of Norway makes the costs of travelling a significant burden. In North Norway in particular, the population is scattered throughout a large geographic area, making the cost of travel to a specialist examination considerable. The specialists are mainly located in a few main cities. New regulations requiring each hospital to cover travel expenses have resulted in a stronger focus on these costs in recent years. At present, 5% of the total budget of the Regional Health Authority of North Norway is spent on travelling/transportation. The cost of travelling was earlier funded by the Norwegian Insurance Administration. If a follow-up programme (i.e. clinical examination and medical history) can be run by the patient's GP, there are obvious reasons to believe that the total costs of such a programme could be reduced.

Whereas there is evidence of survival gain related to intensive follow-up programmes, the burden of cost to the health care service is considerable [26-28]. Renehan et al. published a study in 2004 arguing that intensive follow-up after curative resection for colorectal cancer is economically justified and should be standard practice [29]. However, a Danish study concludes the opposite, stating that follow-up after colorectal cancer surgery is not cost-effective compared to several other procedures, including screening for CRC [21]. The cost-effectiveness of the Norwegian guidelines was documented cost-effective in a prior study when applied in a model-based study implementing data from the literature. The basic cost of the NGICG recommended programme was GBP£ 1,232 per patient. Including extended investigation due to suspected relapse in 45% of cases, the figure rose to £ 1,943 per patient [30]. However, Korner et al [23] argue against this study. The total programme cost in this study was Euro € 228,117 (US 280,994 dollars), translating into € 20,530 (US 25,289 dollars) for one surviving patient after salvage surgery. This cost is less than the one calculated by Norum, but the costs are calculated at different times and in different settings, making a direct comparison useless. Costs are hard to compare with publications from other countries because of different reimbursement policies. Finally, they [23] argue whether the continuing implementation of such a program and costs are justified should be further debated.

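### Hospital is neither a stratification factor nor clearly a named covariate in this four-hospital trial, which leaves avoidable between-hospital noise, mainly in the cost comparison

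*Protocol article*

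**What the plan says.** **Allocation.** Randomization section: "Patients are stratified according to the Dukes's staging and whether they have a stoma". Allocation is through a central web-based service, and no other factor is given.

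**Sites.** Hospitals section: "The University Hospital and these three local hospitals consented to participate". Volumes are unequal. For the local sites: "Three hospitals (located in the cities of Harstad, Mo, and Bodø) have an annual volume of more than 20 colon cancer procedures". For the University Hospital, of the suspected colorectal cancers operated on each year, "approximately 60 of them have a colon cancer disclosed".

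**Control care.** Patients attend their own hospital's surgical outpatient clinic. Control arm section: "This follow-up is performed by consultants or internship doctors in digestive surgery".

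**Cost.** The abstract makes cost a primary endpoint and Objectives puts it in the primary objective. Travel and production losses are among the cost elements (QOL questionnaires, Economic analysis, Analysis). The Discussion says of North Norway that "the population is scattered throughout a large geographic area, making the cost of travel to a specialist examination considerable".

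**Adjustment.** The Analysis section foresees covariate adjustment in general terms, in line with CONSORT. Its list of potential covariates includes cost, satisfaction and QoL measures attached to the outpatient clinic and to the GP practice. These are quantities measured after allocation, and the list does not clearly name the identity of the hospital.

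**The concern.** Hospital is known for every patient before randomisation and could plausibly predict cost. It fixes where the control patient's clinic is, and the protocol itself presents travel as a main economic reason for GP follow-up. With allocation balanced only on stage and stoma, the hospital mix of the two arms is left to chance. Unless the analysis uses hospital, any between-hospital variation stays in the error term. The Sample size section bases its calculation on QoL and states no power for cost, so avoidable noise in the cost comparison deserves some attention.

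**Working it through.** **Inputs from the protocol.** Four hospitals; about 60 colon cancers a year at the University Hospital and more than 20 at each local one; target difference 10 and SD 20 on global QoL; dropout 20%; total 170. On error rates: "Alpha and beta were set at 0.05 and 0.2 respectively and tests were two-sided".

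**Assumptions.** 1:1 allocation (the ratio is not stated). Site shares 60:20:20:20, that is 1/2, 1/6, 1/6, 1/6. The share of variance due to hospital is not in the documents, so a range is used.

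**The plan's sample size.** n per arm = 2 × (1.96 + 0.84)² × 20² / 10² ≈ 63, so 126 in total, and 126 / 0.8 ≈ 158. With a t-test it is 64 per arm, 128 / 0.8 = 160. The stated 170 is not reproduced by these formulas, but it errs on the safe side: 170 × 0.8 = 136 evaluable, 68 per arm, gives 83% power. Nothing below depends on the discrepancy.

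**How uneven the arms may be by hospital.** With 85 per arm, the between-arm difference in University Hospital share has SD √(2 × 0.5 × 0.5 / 85) ≈ 7.7 percentage points (7.6 in simulation). In 40,000 simulated trials it exceeded 10 points in about 19% and 20 points in 0.7%. With equal site shares these become 13% and 0.2%.

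**Effect on global QoL.** Standard error of the difference = 20 × √(2/68) = 3.43 points. If hospital explains a share s of the variance, the chance shift has mean 0 and SD = √s × 3.43. Simulation with 68 per arm, 6,000 runs per setting:

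| s (assumed) | SD of shift | 95th percentile of shift | Type I error, unadjusted | Power, unadjusted | Power, hospital adjusted |
|---|---|---|---|---|---|
| 1% | 0.34 | 0.66 | 5.3% | 82.4% | 81.9% |
| 5% | 0.77 | 1.52 | 5.4% | 83.4% | 84.1% |
| 10% | 1.08 | 2.15 | 4.7% | 82.2% | 85.0% |

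At s = 20% and 40% the unadjusted type I error was 4.8% and 5.0%. The simulation error of each rate is about √(0.05 × 0.95 / 6,000) = 0.3 percentage points, so all are compatible with 5%.

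**Effect on cost.** No SD for cost is given, so the shift can be expressed only in standard errors: √0.10 = 0.32 and √0.40 = 0.63, or about 0.3-0.6 for s of 10-40%. Removing that variance is worth at most 1 / (1 − 0.10) = 1.11 to 1 / (1 − 0.40) = 1.67 times the sample size for this comparison. Both figures assume that hospital acts alike in the two arms. If it acts mainly through clinic visits in the control arm, a common hospital term recovers less.

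**Cell sizes.** Now 3 stages × 2 stoma levels = 6 cells, 170 / 6 = 28.3 patients each. With hospital, 24 cells, 170 / 24 = 7.1 each.

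**The case against.** A reader might infer that imbalance by hospital can drive the cost and QoL results. One calculation seems to support this. With sites of 85, 28, 28 and 28, the chance of a split of 60:40 or worse is about 34% at a given local hospital and 8% at the University Hospital, and about 74% for at least one of the four. That counts splits, not their effect. At a site of 28 such a split is 17 against 11, or 17/85 = 20% against 11/85 = 13% of the arms. Even if that site's mean differed from the rest by a full SD, the arm difference would move by about 0.07 SD, under half of its standard error of √(2/85) = 0.15 SD. Under valid randomisation this variation is already in the standard error, as the type I error rates confirm.

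A reader might also infer that clinician grade or travel distance differs by hospital. The protocol does not say so. It names two grades of clinician without tying them to sites, and it attributes travel cost to a scattered population with specialists in a few cities. Distance also varies within a catchment, so balance on hospital would balance travel only in part. Differences between clinicians at the control clinics arise after randomisation and belong to the comparator; stratification would not remove them.

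The choice of factors is defensible too: stage and stoma plausibly predict QoL, the outcome that set the sample size, and a third factor thins the cells. Finally, a condensed article may leave model terms to a full protocol or analysis plan that is not shown.

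All of this stands, and it limits the point to precision. It does not remove the point: the stratification factors are stated outright, and hospital is a baseline factor that costs almost nothing to use.

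**Conclusion.** The point holds as a minor one about precision. Stratification omits hospital, and the covariate list does not clearly include it. The comparison remains unbiased with nominal type I error. For QoL the loss is small: a 95th percentile shift of about 0.7-2.2 points against a target of 10, if hospital explains 1-10% of the variance. For cost it could be larger, with a shift of SD about 0.3-0.6 standard errors if hospital explains 10-40% of the variance. Those shares are assumptions, as are the site proportions and 1:1 allocation. The documents contain no cost or QoL figures by hospital that would confirm or narrow them. The absence of a hospital term from a condensed article is not in itself counted as an error.

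**What to change.** State in the analysis plan, before the arms are compared, that the between-arm QoL and cost models include hospital as a fixed effect with four levels, alongside Dukes's stage and stoma. The hospital term costs 3 degrees of freedom, recovers nearly all the precision that stratification would give, and works for patients already randomised. If a fuller plan already contains this term, nothing more is needed.

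Optionally, if recruitment allows, add hospital as a factor in the central web-based allocation, by a method suited to about 7 patients per cell, such as minimisation with a random element. This is more debatable: it changes the allocation procedure, possibly in mid-trial and where clinic and patient know the arm, for little gain beyond the model term. The article does not describe the present allocation method or the service's options, so the effort of changing it cannot be judged from the document.
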